##### Characteristics of patients succeeding in PPI deprescribing

Association of patient characteristics (age, sex, socio-economic status, chronic disease, GP) and PPI deprescribing success will be tested with a generalized linear mixed model to account for the random effect of GP’s practice.

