### Data collection procedures

Baseline patient variables (age, sex, PPI reimbursement, chronic disease, free complementary health insurance for economically vulnerable patients) and GP variables (age, sex, activity type and city classification) will be collected using the local health insurance reimbursement database (SIAM-ERASME) (Fig. 2).

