### Sample size and power

Preliminary analyses showed that around 33,000 patients, 1300 GPs and 684 practices would meet inclusion criteria in 2017, which corresponds to a mean of 1.9 GPs and 48.3 patients per practice. Using an intraclass correlation coefficient (ICC) of 0.05 thus lead to an inflation factor of 3.365. Literature data suggested a “natural” PPI deprescribing rate between 2 and 7% in the control arm [17, 20, 30].

Assuming an inflation factor of 3.365 and using a two- sided alpha of 0.05, we will have 90% power to detect a minimum true difference of 9.5% of PPI deprescribing rates between the multi-faceted intervention arm and the control arm. These estimates change slightly if different natural deprescribing rates and higher ICCs are assumed (Table 1).

**Table 1 Tab1:** Sample size simulation

“Natural” PPI deprescribing rate	PPI deprescribing rate due to intervention	Patients per cluster	Intracluster Correlation Coefficient	Power
2%	17%	45	0.05	> 0.999
2%	17%	50	0.05	> 0.999
2%	17%	45	0.1	> 0.999
2%	17%	50	0.1	> 0.999
2%	10%	45	0.05	> 0.999
2%	10%	50	0.05	> 0.999
2%	10%	45	0.1	> 0.999
2%	10%	50	0.1	> 0.999
7%	17%	45	0.05	> 0.999
7%	17%	50	0.05	> 0.999
7%	17%	45	0.1	> 0.999
7%	17%	50	0.1	> 0.999
7%	10%	45	0.05	> 0.994
7%	10%	50	0.05	> 0.990
7%	10%	45	0.1	> 0.930
7%	10%	50	0.1	> 0.908

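### The analysis of who succeeds tests 'GP' with only a practice random effect, so GP variables that differ within a practice may get standard errors that are too small

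*Protocol article*

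**What the plan says.** In the protocol article, the section *Characteristics of patients succeeding in PPI deprescribing* states: "Association of patient characteristics (age, sex, socio-economic status, chronic disease, GP) and PPI deprescribing success will be tested with a generalized linear mixed model". The sentence ends by giving the reason for the mixed model: "to account for the random effect of GP’s practice". No other random effect is named there, and the word 'GP' in the list is not defined.

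*Data collection procedures* shows what is recorded about the GPs: "GP variables (age, sex, activity type and city classification) will be collected using the local health insurance reimbursement database".

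*Sample size and power* gives the structure of the data: "around 33,000 patients, 1300 GPs and 684 practices would meet inclusion criteria in 2017", that is, "a mean of 1.9 GPs and 48.3 patients per practice". The only clustering parameter is set per practice: "Using an intraclass correlation coefficient (ICC) of 0.05 thus lead to an inflation factor of 3.365". No ICC is given for GPs within a practice.

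**The concern.** Patients are nested in GPs, and GPs in practices. A model with only a practice intercept treats the patients of one GP as independent once the practice is known. That does no harm for a covariate that is constant within a practice, because the practice intercept absorbs the clustering. It does harm for a covariate that differs between two GPs of the same practice. If those GPs also differ in how much they deprescribe, for reasons unrelated to the covariate, the roughly 25 patients of each GP are counted as separate evidence on that GP's age or sex.

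The second difficulty is the undefined word. If 'GP' means the identity of the GP, entered as a fixed factor, the model has about 1,300 levels nested inside the practice effect.

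At stake is one item in a secondary, associational analysis: associations with GP characteristics could be declared more often than the nominal 5%.

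**Working it through.** **Inputs from the article.** 33,000 patients, 1,300 GPs and 684 practices; practice ICC 0.05; two-sided alpha 0.05; control-arm deprescribing rate 2% to 7%. Patients per GP: 33,000 / 1,300 = 25.4. GPs per practice: 1,300 / 684 = 1.9.

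**The plan's own figure.** Inflation factor = 1 + (48.3 - 1) × 0.05 = 3.365, which matches. The ICC is therefore a practice-level quantity. The article states no error rate for the analysis in question, so there is none to reproduce.

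**Assumption.** The ICC between GPs within a practice is not given. It is varied here from 0 to 0.05.

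**Closed form, for a covariate that varies only within practices.** The true variance exceeds the model's variance by the ratio VR = 1 + (25.4 - 1) × ICC_GP. The false-positive rate is 2 × [1 - Φ(1.96 / √VR)].

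- ICC_GP 0.01: VR = 1.244, rate 7.9%
- ICC_GP 0.02: VR = 1.488, rate 10.8%
- ICC_GP 0.03: VR = 1.732, rate 13.6%
- ICC_GP 0.05: VR = 2.219, rate 18.8%

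This is an upper bound for the real case, where a GP variable varies both within and between practices.

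**Simulation.** 684 practices, 1.9 GPs per practice on average (spread over practices in two different ways), 25 patients per GP, a null binary GP covariate and a linear mixed model with a practice intercept only; 6,000 runs per setting. Ranges cover the two layouts.

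| GP ICC | Practice ICC | False-positive rate |
|---|---|---|
| 0 | 0.05 | 5.0% |
| 0.01 | 0.04 | 6.8-7.0% |
| 0.01 | 0.05 | 7.2-7.7% |
| 0.02 | 0.03 | 9.5-9.8% |
| 0.02 | 0.05 | 10.0-10.1% |
| 0.03 | 0.02 | 11.9-12.0% |
| 0.04 | 0.01 | 12.8-14.2% |
| 0.05 | about 0 | 14.1-15.1% |
| 0.05 | 0.05 | 17.4% |

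A covariate constant within the practice gave 5.2% and 5.5% (GP and practice ICCs 0.02 and 0.03, then 0.05 and 0.05). The excess therefore comes from the missing GP level.

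**Logistic check.** This used success rates of 7% and 17% and 400 runs per setting, so it is coarser. With the ICCs read roughly on the probability scale, the rate was 10-13% at GP ICC 0.02 (practice 0.03) and 17-27% at 0.05 (practice 0.05). With the ICCs read on the latent scale, it was 5.5-7% and 9-10.5%. The article does not say which scale its ICC is on.

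**GP identity as a fixed factor.** About 1,300 dummies exhaust the between-practice information, so the practice variance is not identified, and single-GP practices are fully aliased. A GP with no success has no finite log-odds. With 25.4 independent patients, the chance of this is 0.93^25.4 = 16% at a 7% success rate and 0.98^25.4 = 60% at 2%. Applied to all 1,300 GPs for illustration, that is about 206 and 778. These are control-arm rates; at 10% the chance is 0.90^25.4 = 7%, or about 89 GPs.

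**The case against.** The strongest objection is that this is a condensed article and one sentence on a secondary analysis. It names the practice random effect without saying that it is the only one, and an analysis plan could define 'GP' and add a level. That limits the weight of the point but does not remove it: the sentence itself puts 'GP' among the tested covariates and gives the model a practice effect only, so a plan that repeats it carries the defect.

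Three further objections stand.

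- The aim and outcome sections speak of patient characteristics, and four of the five listed items (age, sex, socio-economic status, chronic disease) are at patient level. No inflation is shown for them.
- City classification, if shared by a practice, keeps its size. In single-GP practices the practice effect absorbs the GP effect.
- Every rate above 5% depends on a within-practice GP variance that the article does not give.

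A reader might infer more than this. One might take a false-positive rate of 10% to 20% as established; it is not, since the range starts at 5%. One might conclude that a GP effect cannot be estimated; that holds only for identity as a fixed factor, which the article does not specify, and as a random effect nested in practice it is estimable from the practices with several GPs. One might suppose that the analysis would decide which GPs to target in a wider programme; the conclusion of the article ties wider use to the effectiveness of the intervention and says nothing of selecting GPs.

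**Conclusion.** The point holds in conditional form and is minor. If 'GP' means the recorded GP variables, the model as worded understates the standard errors of those that vary within a practice whenever GPs of one practice differ in deprescribing. The size rests on the assumed GP ICC and on the linear simulation above: correct size at zero, modest excess at 0.01 to 0.02, and roughly three times the nominal rate at 0.05. The logistic check shows that the scale of the ICC moves these figures in both directions. The comparison of arms in the primary analysis is essentially unaffected, because arm is assigned by practice and does not vary within it.

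**What to change.** In *Characteristics of patients succeeding in PPI deprescribing*, replace the bare 'GP' with the GP variables listed under *Data collection procedures*, enter them as fixed effects, and add a random intercept for GP within practice beside the practice intercept. State that GP identity is not entered as a fixed factor.

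The cost is one extra variance term and a change of wording, with no new data. Intervals for GP-level associations become wider. For a purely within-practice covariate the closed form puts the widening at about √1.244 = 1.12 times at GP ICC 0.01 and √2.219 = 1.49 times at 0.05; there is none if the GP variance is zero.

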### Missing data

For the primary outcome analysis, data for patients lost to follow-up (i.e. death, moving outside the study region, or disaffiliation from the French health national insurance system) will be managed by a multiple imputation method (Generates Multivariate Imputations by Chained Equations) [34]. Patient characteristics used for this imputation will be the variables associated with the primary outcome or associated with the presence of missing data on the primary outcome. A sensitivity analysis will be performed by removing these patients from the analysis.

### Timeframe

Trial baseline will be planned in mid-November 2020 when deprescribing materials will be mailed to patients and GPs. The three patient reported outcome questionnaires will be mailed 1 month before and 12 months after baseline, mid-October 2020 and mid-November 2021 respectively. Data will be collected 12 months after baseline in mid-November 2021. Study schedule is detailed in the SPIRIT diagram (Table 2).

**Table 2 Tab2:**
[figure not shown]
Study schedule (SPIRIT diagram of trial stages of enrolment, intervention, outcome assessment and evaluation)

### Ethics approval

This protocol has received ethics approval from the *Collège National des Généralistes Enseignants* ethics committee (#08062011).

## Discussion

### Study rationale

This trial will assess the effectiveness of three PPI describing strategies, with a view to applying them to deprescribing other medicines. In 2015, Clyne et al. reported that a multi-faceted intervention involving patient education materials for deprescribing reduced potentially inappropriate prescriptions in primary care by 25% more than control group, with a sustained effectiveness 1 year later [18]. In 2017, the multi-faceted Australian national quality improvement programs that also included patient education material contributed to reducing PPI use in older adults by 21% [19]. In 2020, several interventional cycles in the United-States included patient education pamphlets and discontinued inappropriate chronic PPI use by 30% within 12 months [20]. Based on these previous studies in Australia, Ireland and United-States, we anticipate that involving patients in the deprescribing process using an education brochure should improve the PPI deprescribing rate.

### Strengths and limitations

#### Strengths

Using the PRECIS-2 tool, 6 out of the 9 domains of the multi-faceted intervention fall into the pragmatic side of the pragmatic-explanatory continuum (supplementary material 3). The pragmatic approach involves intervention at the group level rather than the individual level and as such, cluster-randomizations are the most common in pragmatic trials [35]. Also, cluster-randomization are considered as the most appropriate to conduct deprescribing trials [36].

Our trial involves a large number of patients and GPs. It is, to our knowledge, the first population-based deprescribing trial in France. We expect to exhaust the eligible population ensuring a high statistical power for a minimal difference.

By using a 3-arm design, we will be able to assess which intervention is the most effective. The single intervention on GP versus usual care will detect the effectiveness of mailing the PPI deprescribing algorithm to GP. The multi-faceted intervention will measure an additional or a combined effect of the patient education brochure.

#### Limitations

Despite these strengths, our trial has several limitations. Firstly, regarding the deprescribing rate and the cost-utility analysis, our data will be collected from the health insurance reimbursement database. This database only estimates the consumption of medications through their reimbursements [37]. PPI consumption can be overestimated because real patient intake depends on adherence. Conversely, this database does not compile over-the-counter PPI but they are less used than reimbursable PPI [38].

Secondly, the secondary outcome on GERD recurrence is assessed by the GERD impact scale questionnaire at 12 months after baseline. Thus, we may miss GERD recurrence caused by an early acid rebound due to PPI withdrawal. However, sending this questionnaire during the intervention may influence patients’ perceptions, resulting in a participation bias on the primary outcome. We chose to keep our trial without further interventions during the study period. The GERD impact scale will only assess the GERD recurrence following PPI deprescribing.

Thirdly, neither patients nor their GP will be blinded because of the pragmatic trial design [39]. However, the participants will not be informed of the different interventions occurring during the year of the trial. Data managers and statisticians will be blinded to the allocation arm. Primary outcome (PPI deprescribing) is objective and not subject to interpretation.

Fourthly, because of logistical constraints, only a 10% sample of the population (nearly 3300 patients) will have the opportunity to answer questionnaires on secondary outcomes. The questionnaires will be sent by mail and the number of participants will depend on response-rate. However, the response-rate should be increased due to pre-paid return envelopes and amplified by phone reminders, as reported by Neve et al. for patient reported outcomes [40].

## Conclusion

Our trial is expected to demonstrate the effectiveness of the multi-faceted intervention involving both a patient education brochure and a personalized letter to GPs containing a PPI deprescribing algorithm. If so, this multi-faceted strategy for PPI deprescribing could be implemented more widely at the national level and for other potentially inappropriately prescribed medications.

### Trial status

First submission on ClinicalTrials.gov was February 5th 2020 and patient data are currently being collected from SNDS until the end of 2022.

### Adherence to reporting guidelines

The authors used the Standard Protocol Items: Recommendations for Interventional Trials (SPIRIT) checklist when they wrote this protocol [41] (Additional File).

## Data Availability

Data sharing is not applicable to this article as no datasets were generated or analyzed during the current study yet.

## Abbreviations

DDD: Defined Daily Dose
GERD: Gastroesophageal Reflux Disease
GP: General Practitioner
ICC: Intracluster Correlation Coefficient
ICUR: Incremental Cost-Utility Ratios
mITT: Modified Intention-To-Treat
NSAIDs: Nonsteroidal Anti-Inflammatory Drugs
PPI: Proton Pump Inhibitors
QALY: Quality-Adjusted Life-Years
rPATD: Revised Patients’ Attitudes Toward Deprescribing
